##### Functional performance

The execution of YBT, carried out as described above, will also be computed for each direction, anterior, postero-medial, and postero-lateral, displacement, in centimeters, performed with contralateral limb to supporting member [25] (Fig. 4). Average displacement (AD) in each direction will be normalized using the length of support leg (LS) of the individual [25], and composite score (CS) will be calculated.

CS = AD (ant + postero-medial + postero-lateral)/3 × LS (×100)

To evaluate functional performance of THT, a demarcation will be carried out, consisting of a line 6 m long and 15 cm wide, perpendicular to a starting point [27].

This test is used to measure the combination of muscle strength, neuromuscular control, and ability to tolerate sports-related activities [28]. The participant must perform 3 maximum jumps with the same leg following the trajectory of the marked line. Subsequently, the distance between starting line and the tip of Hálux at the site of the last landing must be measured in centimeters [27] (Fig. 5). Three (3) repetitions will be carried out for the member to be tested, and the best result will be computed for later analysis.

**Fig. 5 Fig5:**
[figure not shown]
Triple hop for distance test scheme

##### Satisfaction

At the end of data collection after final reassessment (3–4 after applying technique), the Medrisk [9] satisfaction questionnaire will be presented, which is an instrument used to evaluate patient's satisfaction with physiotherapy treatment, composed of 13 questions with scores from 1 to 5 evaluating the quality of service and, 1 question evaluating one’s clinical perception of performance improvement.

### Statistical analysis

The normality test will be performed using the Kolmogorov Smirnov test. If null hypothesis is confirmed, comparison between groups will be performed using parametric tests, however, if null is not confirmed, non-parametric tests will be applied.

For parametric data, the effect of treatment will be evaluated by ANOVA two-way test for repeated measurements, considering a value of *p* ≤ 0.05. Data will be evaluated by intention to treat, through the imputation of the missing data using the *multipleimputation* method. For non-parametric data, the Kruskal-Wallis test will be used. All tests will be calculated using SPSS.

Clinical relevance of results will be confirmed by calculating the effect size (Cohen’s *d*) of significant differences found between assessments. The following effects will be considered: 0.00–0.49, small; 0.50–0.79, medium and above 0.80, large. Analysis of data will be made by intention to treat [29].

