### Primary objective

To evaluate the immediate and short-term effect of the associated joint mobilization techniques, Mulligan concept and Maitland method, for the ankle joint, on range of motion.

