### Participants and evaluators

Sample calculation was performed using a difference of means and standard deviation, based on closed kinetic chain range of motion, of similar works, being RoM of DF in CKC, primary outcome, performed through the lunge test (LT), and minimum clinically relevant difference of 3.8 degrees [20], with an estimated standard deviation of 4.4°, and considering ANOVA statistical test of repeated measurements. The protocol considered a 0.05 alpha level and an 80% statistical power, being a sample size of 23 volunteers per group. A possible sample loss (15%) was computed, a total of 54 volunteers was considered for randomization.

Eligibility criteria are as follows: men and women between the ages of 18 and 40 will be recruited who have a range of motion (RoM) in closed kinetic chain of less than 40°, verified by lunge test. If the volunteer has bilateral ankle dorsiflexion limitation, the most affected side will be considered for analysis and intervention.

Exclusion criteria are as follows: presenting musculoskeletal injury in the lower limb, rheumatic diseases, cardiovascular diseases, dizziness, vertigo or changes in the vestibular system, neuropathic problems, or any other alteration that could harm the volunteer’s health or compromise performance of tests.

These individuals will be recruited through posters on the campus of the Federal University of Uberlândia (UFU) and by dissemination on social media and local media (TV and radio). So as to increase adherence, especially in the post-intervention evaluations, the volunteers will receive orientation, after final evaluation (A2), as to perform the exercises to maintain or improve ankle RoM.

Research will be developed at the Laboratory of Evaluation in Biomechanics and Neurosciences (LABiN) of the Faculty of Physical Education and Physical Therapy of the Federal University of Uberlândia, Minas Gerais, Brazil.

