#### Primary outcome

The primary outcome corresponds to DF ankle range of motion in CKC measured through lunge test (LT).

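### The planned unadjusted repeated-measures ANOVA treats the baseline angle as an outcome; a baseline-adjusted between-group contrast would use the same data better, and the stated 80% power cannot be tied to any ANOVA term

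*Protocol article*

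**What the plan says.** Under Statistical analysis, for data judged parametric, "the effect of treatment will be evaluated by ANOVA two-way test for repeated measurements", at a 0.05 level. No covariate is named. Outcome measurements lists three assessments: A0 before the intervention, A1 immediately after it, and A2 three to four days later. The natural reading is a two-group by three-time layout in which A0 is one level of time.

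Under Participants and evaluators, "Sample calculation was performed using a difference of means and standard deviation": 3.8 degrees on the lunge test, "with an estimated standard deviation of 4.4" degrees, alpha 0.05 and 80% power, giving 23 per group, "and considering ANOVA statistical test of repeated measurements". No within-person correlation, number of measurements or ANOVA term is given there.

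The Primary objective is "To evaluate the immediate and short-term effect of the associated joint mobilization techniques" on range of motion, so A1 and A2 stand side by side. The Background states the hypothesis as a comparison: the two techniques together against the Mulligan technique alone.

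**The concern.** A two-way repeated-measures ANOVA gives three tests: group, time and group-by-time. None is a direct estimate of what the second technique adds at A1 or at A2.

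- The group term averages over A0, A1 and A2. Randomisation makes the expected A0 difference zero, so a sustained effect is averaged down to two thirds.
- The group-by-time term is a 2-df omnibus test. It shows that the profiles differ somewhere, but not at which visit.
- The time term is change in two arms that both receive mobilisation. It has no untreated comparison and does not bear on the added effect.

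A0 is scheduled for every participant and would do more as a covariate. The sample-size paragraph also names the ANOVA family without the inputs that power for such a test needs. A reader therefore cannot tell which comparison has 80% power.

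**Working it through.** **Inputs.** From Participants and evaluators: difference d = 3.8, SD s = 4.4, n = 23 per group, alpha 0.05 (taken as two-sided). From Outcome measurements: three assessments. Assumed, because the article does not give them: within-person correlation rho, equal between all pairs of visits; s is the SD of a single measurement; d is the same at A1 and A2 unless stated otherwise.

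**The plan's own figure.** A two-sample t-test on 3.8/4.4 has 79.9% power at 22 per group and 81.7% at 23. The smallest n reaching 80% is therefore 23, the stated figure. Other routes also lead there:
- the interaction at rho of about 0.43 to 0.45;
- the group term at rho of about 0.17 to 0.20;
- a change-score comparison at rho 0.5, where the SD of change, s√(2(1 − rho)), equals s.

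**Group term.** The estimate averages differences of 0, 3.8 and 3.8, giving 7.6/3 = 2.53. The SD of a person's mean is s√((1 + 2rho)/3). At rho 0.5 this is 4.4 × √(2/3) = 3.59, so SE = 3.59 × √(2/23) = 1.06.

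**Interaction.** The deviations from 2.53 are −2.53, 1.27 and 1.27, with sum of squares 9.63. The noncentrality is (n/2) × 9.63 / (s²(1 − rho)). At rho 0.5 this is 11.5 × 9.63 / 9.68 = 11.4, on 2 and 88 df.

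**A0-adjusted contrast at one visit.** The residual SD is s√(1 − rho²), on 43 df.

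**A0-adjusted mean of A1 and A2.** The residual SD is s√((1 + rho)/2 − rho²). This is the like-for-like counterpart of the group term.

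Power at 23 per group:

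| Test | rho 0.1 | 0.3 | 0.5 | 0.7 |
|---|---|---|---|---|
| Group term, A0 included | 86% | 74% | 65% | 57% |
| Interaction, effect sustained | 60% | 71% | 85% | 98% |
| Interaction, A2 effect halved to 1.9 | 47% | 58% | 73% | 93% |
| A0-adjusted, one visit | 82% | 85% | 91% | 98% |
| A0-adjusted, mean of A1 and A2 (sustained) | 97% | 97% | 98% | >99% |

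The group term reaches 80% only for rho below about 0.20. The interaction reaches it only for rho above about 0.43, or above about 0.57 if the A2 effect halves. Between 0.20 and 0.43 neither does. The adjusted one-visit contrast stays at about 82% or more at every rho.

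**Precision.** The planned ANOVA does use A0, through change, so the fair comparator is the change-score SE, 4.4 × √(2(1 − rho)) × √(2/23). The adjusted SE is 4.4 × √(1 − rho²) × √(2/23).
- rho 0.5: 1.30 for change, 1.12 adjusted.
- rho 0.7: 1.005 for change, 0.93 adjusted.

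**The case against.** The defence has force on several points.

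- A reader might infer that the 80% was computed for a different test from the one planned. The article does not support that as a fact. The sample-size paragraph names the same ANOVA family, 23 per group follows from several assumptions, and the text does not say whether 4.4 is the SD of a measurement or of change.
- A reader might infer that the trial is underpowered. That is not shown. The interaction, the usual treatment term in this design, has 85% at rho 0.5 and 98% at 0.7 with a sustained effect. At rho 0.1 the group term (86%) even exceeds the adjusted one-visit contrast (82%).
- A reader might infer that a significant time effect could be declared a positive result. The Background hypothesis is between groups, and the analysis section speaks of comparing groups. What remains is loose wording, where Cohen's d is attached to significant differences across assessments.
- A one-visit contrast and a 2-df test of the whole profile answer different questions, so their powers are not strictly rivals.
- An analysis plan not shown may name the deciding term, so its absence from a condensed article is not held against the trial.

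One part of the point survives all of this. The article itself fixes an ANOVA with no covariate and ties its power to that family. For the stated hypothesis, baseline adjustment uses the same data more efficiently.

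**Conclusion.** The concern holds as a matter of efficiency and clarity. The planned analysis is valid, and leaving out the covariate introduces no bias. Its power at 23 per group with a sustained effect, for rho from 0.1 to 0.7, runs from 57% to 86% on the group term and from 60% to 98% on the interaction. The A0-adjusted one-visit contrast has 82% to 98% over the same range. Against a change-score comparison, adjustment lowers the standard error by about 14% at rho 0.5 (1.12/1.30 = 0.86) and about 8% at rho 0.7 (0.93/1.005 = 0.92).

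The stated 80% cannot be tied to any term of the planned ANOVA. The inputs shown match a two-sample comparison at one visit, but do not prove that this was the method. All ANOVA and adjusted figures rest on an assumed rho with equal correlation between visits, and on reading 4.4 as the SD of a single measurement.

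**What to change.** Analyse the lunge-test angle at A1 and A2 in a linear mixed model with group, visit, group-by-visit and the A0 angle as covariate, or by ANCOVA at each visit. Base the conclusion on the B minus A contrast and report time effects descriptively.

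The sponsor should choose how A1 and A2 share the 0.05 level: one primary visit, a fixed order, or a joint test. The Primary objective gives the two horizons equal standing. One primary visit or a fixed order gives some of that up, whereas a joint test keeps it. The one-visit powers above assume the full 0.05 at that visit, so power should be restated for the option chosen.

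In the sample-size paragraph, state which contrast the 80% refers to and the correlation assumed. If that is how it was obtained, say instead that the figure is a conservative two-sample calculation at one visit.

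The cost is a change of wording and the choice about the two visits. No further participants, measurements or assessments are needed.

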## Subjects and methods

### Study design

This study is a randomized, controlled, blind clinical trial with two parallel groups (Fig. 1). The study was approved by the Human Rights Ethics Committee under protocol number CAAE: 30660520.1.0000.5152 and registered in the Brazilian Registry of Clinical Trials (ReBEC) (registration number: RBR-93xv9t). Recruitment will begin in September 2020 with a probable end date of November 22, 2021, as a result of the pandemic in the country*.* According to the flowchart (Fig. 1), evaluations will be conducted pre-intervention (A0), post-intervention (A1), and 3–4 days after intervention (A2). Variables to be observed are: Amplitude of Motion of Dorsiflexion of ankle in 20 closed kinetic chain and open kinetic chain, postural balance, and functional performance.

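### A normality pre-test can switch the three-visit outcomes to Kruskal-Wallis, which is not the rank counterpart of the repeated-measures ANOVA it replaces

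*Protocol article*

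**What the plan says.** The Study design section describes a "randomized, controlled, blind clinical trial with two parallel groups" in which "evaluations will be conducted pre-intervention (A0), post-intervention (A1), and 3–4 days after intervention (A2"). The Primary outcome section fixes the lunge test angle: "The primary outcome corresponds to DF ankle range of motion in CKC measured through lunge test (LT").

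The Statistical analysis section then sets a two-branch rule:

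- **Gate:** "The normality test will be performed using the Kolmogorov Smirnov test".
- **If the gate is passed:** "If null hypothesis is confirmed, comparison between groups will be performed using parametric tests". For such data "the effect of treatment will be evaluated by ANOVA two-way test for repeated measurements".
- **If it is not passed:** "if null is not confirmed, non-parametric tests will be applied". The only such test named is in this sentence: "For non-parametric data, the Kruskal-Wallis test will be used".

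The section does not say whether the normality test is run on raw values or residuals, or whether Kruskal-Wallis is applied to all visits, to one visit or to change from A0. No outcome is exempt, including the primary one.

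**The concern.** The hypothesis in the Background section is an additional effect of the combined techniques over Mulligan mobilisation alone, both immediately and at 3–4 days. With three measurements per volunteer, that is a between-group difference in change, which the repeated-measures ANOVA addresses through its group-by-time term. Kruskal-Wallis has one factor and treats all observations as independent, so an outcome that moves to the fallback branch loses both the within-person structure and the interaction.

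Two things are at stake. First, several uses that the wording leaves open give wrong error rates or answer another question. Both arms receive active mobilisation, so improvement in both is plausible, and that is where a test across all cells misleads most. Second, the branch is chosen by a test on the trial's own data. A non-significant normality test is read as confirmation of normality, which it cannot give at about 27 per group. Different outcomes may then be judged by tests of different hypotheses.

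**Working it through.** **Inputs.** From Participants and evaluators: difference 3.8°, SD 4.4°, alpha 0.05 (two-sided assumed), power 80%, 23 per group, 15% loss, 54 in total. From Study design: two groups, three assessments. Assumed, because the article gives none: within-person correlation r of 0.5 to 0.9, equal between all pairs of visits, with 0.3 added where it matters. The simulations use normal data with 23 per arm.

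**The plan's own figure.** n per group = 2 × (1.960 + 0.842)² × 4.4² / 3.8² = 21.05, so 22. The t-based solution is 22.05, so 23, as stated. Then 23 × 1.15 = 26.45, so 27 per group and 54 in total. The sample size is not in dispute.

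**Use 1: all visits pooled by group.** Three correlated values per person inflate the variance of a group summary by 1 + 2r. The approximate true type I error is P(|Z| > 1.96/√(1 + 2r)).

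- r = 0.5: 1.96/√2.0 = 1.39, giving 17%.
- r = 0.8: 1.96/√2.6 = 1.22, giving 22%.
- r = 0.9: 1.96/√2.8 = 1.17, giving 24%.

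Simulation gives about 17–23% against a nominal 5%.

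**Use 2: three visits compared within one group.** Pairing shrinks the differences between visits by about 1 − r, but the test does not know this. The statistic behaves like (1 − r) times a chi-square on 2 degrees of freedom, so the type I error is about 0.05^(1/(1 − r)). At r = 0.5 that is 0.05² = 0.25%. At r = 0.8 it is 0.05⁵, effectively zero. Simulation gives 0–0.3%. Power for a 2° change is 8–22%, against 46–99% for the Friedman test. This use also does not compare the groups.

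**Use 3: six group-by-visit cells.** If both groups improve by 4° and do not differ, the test rejects in 99–100% of runs. The rejection is correct for the null hypothesis tested (six equal distributions) but says nothing about the added effect of group B.

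**Use 4: the two groups at one visit.** With two groups, Kruskal-Wallis is the Mann-Whitney test. Simulated type I error is about 5%, and power for 3.8° is about 80% whatever r is, because baseline is not used. A rank test on change from A0 works with SD 4.4 × √(2(1 − r)):

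| r | SD of change | Power, change scores | Power, single visit |
|---|---|---|---|
| 0.3 | 5.2° | 66% | about 80% |
| 0.5 | 4.4° | 82% | about 80% |
| 0.8 | 2.8° | 99% | about 80% |

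The two are level at r = 0.5, where √(2 × 0.5) = 1. Above that the single-visit test loses power; below it the change score does. Adjusting for baseline gives a residual SD of 4.4 × √(1 − r²), that is 4.2°, 3.8° and 2.6° at r = 0.3, 0.5 and 0.8. It is never larger than 4.4°.

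**The gate.** For lognormal data (sigma 0.5, an assumed shape) with n = 27, Kolmogorov-Smirnov with estimated mean and SD detects non-normality 3% of the time uncorrected and about 42% with the Lilliefors correction. Shapiro-Wilk detects it 68% of the time. The article does not say which form is used.

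**The case against.** The strongest defence is that the switching sentence is about comparison between groups, so the natural reading of the fallback is a two-group test at A1 or A2. In a randomised trial that is a valid test of the treatment effect. Its power of about 80% for 3.8° equals the planned power. Nothing in the article describes a six-cell or within-group use. This stands, and it limits the point in three ways.

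- A reader might infer that no use of Kruskal-Wallis can test the added effect of group B. That does not follow: the single-visit comparison does so, and its cost is ignoring baseline. Whether that loses power against change scores depends on a correlation the article does not give.
- A reader might infer that the gate almost never detects non-normality. The 3% figure belongs to the uncorrected form only. If that form were used, the fallback would also rarely be reached, which makes the defect less frequent.
- A reader might conclude that Kruskal-Wallis should go altogether. The satisfaction questionnaire is given once, after the final reassessment, and a two-group rank test suits it.

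What the defence does not do is settle the text. The fallback is named as the replacement for a repeated-measures analysis, with no statement of the data it takes, so the valid use is not the specified one. Nor is this detail left to an unseen analysis plan: the article itself fixes both the gate and the test.

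**Conclusion.** Wrong as written, and it should be fixed. The named fallback does not match a two-group, three-visit design, and the gate that selects it is weak. Applied to the repeated data, it gives a type I error of about 17–23% or 0–0.3% instead of 5%, or rejects almost always for a reason unrelated to treatment. Applied between groups at one visit, it is valid but ignores baseline.

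These sizes rest on 23 per arm, SD 4.4°, normal data and equal correlations of 0.5 to 0.9 between visits. The gate figures rest on one assumed skewed shape. The defect lies in a conditional branch with one valid reading, so a reader should not infer that the trial's main analysis or its sample size is invalid on this account. The repeated-measures ANOVA branch is not affected by the choice of fallback test, and the 23 per group reproduces.

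**What to change.** For outcomes measured at A0, A1 and A2:

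- Drop the normality-test switch. Pre-specify one baseline-adjusted model (ANCOVA, or a mixed model with the group effect at A1 and at A2) for every continuous outcome.
- Check the residuals, and use bootstrap or robust standard errors if they are poor.
- As a sensitivity analysis, pre-specify a baseline-adjusted rank analysis (rank ANCOVA) between the groups at A1 and at A2. This is preferable to ranks of change from A0, which lose power when the correlation is below 0.5.

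For the satisfaction score, keep a two-group rank test and say so.

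The cost is a rewording of the Statistical analysis section and a little extra analysis work. Recruitment, assessments and sample size do not change.

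### Clinical relevance is to be confirmed by Cohen's d of significant differences, and the protocol's own 3.8 degree threshold for the primary outcome is not used

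*Protocol article*

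**What the plan says.** Two parts of the protocol article deal with clinical relevance.

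- **Participants and evaluators.** The trial is sized on the lunge test, the primary outcome, using a "minimum clinically relevant difference of 3.8 degrees" "with an estimated standard deviation of 4.4" degrees. The article continues: "The protocol considered a 0.05 alpha level and an 80% statistical power", "being a sample size of 23 volunteers per group". After allowance for loss, 54 are to be randomised.
- **Statistical analysis.** "Clinical relevance of results will be confirmed by calculating the effect size" (Cohen's d) "of significant differences found between assessments". The bands are "0.00–0.49, small; 0.50–0.79, medium and above 0.80, large". The significance criterion is p ≤ 0.05 in a two-way repeated-measures ANOVA.

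The second section does not mention 3.8 degrees. It does not say which band, if any, counts as not relevant, whether d is for a between-group, paired or change-score contrast, or which SD is the standardiser.

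**The concern.** The protocol holds two standards of relevance for the same outcome: an absolute one in degrees, used to size the trial, and a standardised one, used to interpret it. They do not agree, and only the second is written into the analysis.

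The second standard is also conditional on significance. Since d is computed only once p ≤ 0.05 is met and no band is named as not relevant, the rule as written has no stated negative result.

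The wording on which differences receive a d adds a further problem. The hypothesis in the Background is that adding the Maitland technique brings something beyond Mulligan alone. According to the Intervention/control section, both arms receive the Mulligan technique and three days of self-mobilisation, so change over time is expected in both. Entry also requires a lunge angle below 40 degrees, and the more affected side is chosen when both are limited, which invites regression to the mean. A d for change between assessments within an arm would not speak to the added component.

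At stake is whether the trial could announce clinical relevance for a lunge-test difference that its own sample size section treats as too small, or for a change that both arms would show.

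**Working it through.** **Inputs.** From Participants and evaluators: difference 3.8 degrees, SD 4.4 degrees, alpha 0.05 (two-sided assumed, since sidedness is not stated), power 80%, 23 per arm, 54 in total (27 per arm). From Statistical analysis: p ≤ 0.05 and the three bands. The correlation between assessments is not given, so it is varied below.

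**1. The sample size reproduces.** A two-sample comparison with difference 3.8 and SD 4.4 needs 22 per arm by the normal approximation. The exact t calculation gives 22.05, hence 23, with power 0.817. Then 23 × 1.15 = 26.45, rounded up to 27 per arm, or 54. So 3.8 degrees is the difference that the trial was built to detect between groups.

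**2. The two standards on one scale (SD 4.4).**
- Stated threshold: 3.8/4.4 = 0.86.
- Start of large: 0.80 × 4.4 = 3.52 degrees.
- Start of medium: 0.50 × 4.4 = 2.20 degrees.

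Even a result in the large band can lie below the stated threshold.

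**3. Smallest significant d, group comparison at one time point.** d_min = t(0.975, 2n − 2) × √(2/n).
- n = 23: 0.594, and 0.594 × 4.4 = 2.61 degrees.
- n = 27: 0.546, and 0.546 × 4.4 = 2.40 degrees.

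Both exceed 0.50, so significance alone places the result in the medium band or higher, and the label adds nothing to the p value. Observed differences between 2.40 or 2.61 and 3.8 degrees are significant, at least medium, and below the threshold.

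**4. How often this could occur.** In a simulation with a true difference of 1.9 degrees (half the threshold, SD 4.4), 76% of significant results at 23 per arm and 84% at 27 per arm had an observed difference below 3.8 degrees. All were at least medium.

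**5. Other contrasts that the wording allows.**
- Paired change within an arm: minimum d_z = t(0.975, n − 1)/√n = 0.432 (n = 23) or 0.396 (n = 27). Both are small.
- Group difference in change, standardised by the raw SD: minimum = d_min × √(2(1 − ρ)).

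| Assumed ρ | 23 per arm | 27 per arm |
|---|---|---|
| 0.5 | 0.594 | 0.546 |
| 0.6 | 0.532 | 0.488 |
| 0.7 | 0.460 | 0.423 |
| 0.8 | 0.376 | 0.345 |
| 0.9 | 0.266 | 0.244 |

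The minimum falls below 0.50 once ρ exceeds 0.65 (n = 23) or 0.58 (n = 27).
- At 32 per arm (the 64 volunteers named under Intervention/control, a separate inconsistency) the single-time-point minimum is 0.4997, just under the medium band.

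So the band assigned to a significant result depends on a choice of contrast and standardiser that the protocol does not make.

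**The case against.** The strongest reply is that the bands do discriminate under the planned analysis. A reader might infer from step 3 that every significant difference must be labelled medium or large. The documents do not support that. The plan is a repeated-measures ANOVA and d is attached to differences between assessments; step 5 shows that paired and change-score contrasts can be significant and still small. The medium-or-larger result holds only for a group comparison at one time point with 23 to 27 per arm. This part of the objection stands.

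It is also fair that no sentence declares 2.4 degrees clinically relevant or says that 3.8 degrees will be disregarded. The most that can be said is that such differences could be presented as relevant, because the stated rule contains nothing to prevent it.

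Three other tempting readings go too far:
- That non-significant outcomes will have no estimate. The text restricts Cohen's d to significant differences; it does not forbid reporting means or intervals, and an article may leave these to the full plan.
- That d will certainly be computed on pre-post change within arms. The phrase can be read that way, but it is ambiguous.
- That the 3.8 degree argument extends to the secondary outcomes. The figure is given for the lunge test only.

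Finally, d is calculated after the test and alters neither the p value nor the estimate. That is correct and limits the severity. It does not remove the conflict: the rule for interpreting the primary outcome is stated, and it omits the threshold that the same document set for that outcome.

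**Conclusion.** The point holds in a limited form. The protocol states a relevance rule that depends on significance, uses generic bands and leaves aside its own 3.8 degree minimum (d = 0.86). For a single-time-point group comparison with 23 to 27 per arm, observed lunge-test differences from about 2.4 to 2.6 degrees up to 3.8 degrees could be described as clinically relevant. If d is taken on change between assessments, the band may be small, but the contrast may then not address the added Maitland technique.

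The figures in degrees assume an observed SD of 4.4, a two-sided 0.05 test and no baseline adjustment; the change-score figures also rest on an assumed correlation. The remark that both arms receive the Mulligan technique follows the Intervention/control section and the hypothesis; the Abstract names group B by the Maitland method alone.

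This is a rule that is badly fixed, not a detail missing from a condensed article. It affects what the trial may conclude, not its primary test.

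**What to change.** For the lunge test, report the between-group difference (B minus A) in degrees with its 95% CI at A1 and at A2, whether or not it is significant, and interpret both the estimate and the interval against 3.8 degrees. Keep Cohen's d as descriptive only, for the between-group contrast, and name its standardiser.

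An example at 27 per arm and SD 4.4: an observed difference of 3.0 degrees has d = 3.0/4.4 = 0.68 and an unadjusted interval of 3.0 ± 2.40, that is 0.6 to 5.4 degrees. The present rule labels it medium. The revised report would say that a difference is shown, that the estimate is below 3.8 degrees, and that the interval contains values on both sides of it.

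A stricter rule, that the lower confidence limit must reach 3.8 degrees, is not proposed. It would need an observed difference of about 3.8 + 2.40 = 6.2 degrees (27 per arm) or 3.8 + 2.61 = 6.4 degrees (23 per arm), which this trial was not sized for.

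The change is to reporting and needs no new data or participants. Its cost is that some significant results will not be described as clinically relevant. This can happen even when the true difference is 3.8 degrees: in the same simulation, 39% (23 per arm) to 43% (27 per arm) of significant results then had an observed difference below 3.8. That is why the interval must be read along with the estimate.
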